## **6.2.1.2 Missing Data**

Linear mixed models correct for missing responses at random.

## **6.2.2 Methods for the outcome of Patient opinion questionnaire**

### **6.2.2.1 Descriptive Statistics**

The total number of responses per answer will be calculated and presented in a table.

### **6.2.2.2 Missing Data**

Missing data will not be imputed.

## **6.2.3 Methods for changes in urine culture**

### **6.2.3.1 Descriptive Statistics**

The most common bacteria will be showed in a table for both baseline and end of study.

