## 2. OBJECTIVES

The aim of this trial is to compare single use vs reusable catheters in clean intermittent catheterization and to find out if reusing catheters is not less safe and not less efficient as the current single use practice, leading to the following objectives:

Primary Objective:

1. To determine whether reusable catheters are at least not less safe as single use catheters, measured by symptomatic UTIs.

Secondary Objectives:

1. To register hospital admissions due to UTIs or other adverse events due to CIC.
2. To register other adverse events like the number of urethral damage/strictures and kidney/bladder stone formation in both groups.
3. To determine whether reuse of catheters leads to changes of the urine cultures/urinary microbiome (in cooperation with the department of Medical Microbiology).
4. To perform economical evaluation of the cost-effectiveness of single use versus reusable catheters.
5. To explore patients' perspective on ease of use and cleaning of the reusable catheters compared to the single use catheters.
6. To formulate conclusive recommendations for health care providers and re-formulations of existing protocols.

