## 10. STATISTICAL ANALYSIS

### 10.1 Primary study parameters

For analysis of the results, the groups will be stratified for gender and the female patient group will be balanced for pre- and post-menopausal. Data analysis will be performed using SPSS. The primary analysis will be to assess difference between the intervention and the control groups in the sUTI rate and other adverse effects. Descriptive statistics will be used to describe baseline characteristics of participating patients in both groups. Binomial or categorical outcome measures will be analyzed using Chi-square tests and quantitative outcome variables by t-tests or Mann-Whitney U tests. Two-sided p values are calculated.

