### 10.2 Secondary study parameters

Secondary outcome measurements are symptom specific and quality of life related questionnaires (PGI-I, SF-36, EQ-5D-5L), the amount of urethral damage/strictures, kidney/bladder stone formation and changes in urinary culture/urinary microbiome. The ease of use of the catheters and patients' satisfaction will be evaluated by the ISC-Q and the InCaSaQ.

**Cost-effectiveness:** For the purpose of assessing the cost-effectiveness of reusable catheters, data will be collected on medical healthcare utilization, productivity losses and quality of life of patients alongside the clinical trial. In this cost-effectiveness study, incremental costs and incremental effects of reusable catheters over single-use catheters will be assessed, with effects expressed in quality-adjusted life-years (QALYs). The cost-effectiveness study will adhere to the Dutch health economic guidelines. As such, the societal perspective will be adopted, meaning that all costs and effects will be included in the analyses, regardless to whom they accrue. The time horizon of the cost-effectiveness study will be equal to the timeframe of the clinical trial.

Uncertainty concerning the ICER, QALYs and costs will be assessed using bootstrapping, and this uncertainty will be presented graphically with the CE-acceptability curve.

Data on medical healthcare utilization (i.e. volumes) will be collected both through the hospital and by means of the iMTA Medical Consumption Questionnaire (iMCQ). The iMCQ is a generic, non-disease specific, questionnaire to be filled out by the patient, and assesses the use of a variety of medical services. Hospital records can be used to obtain information about consultations and admissions for symptomatic UTIs.

Costs of catheters will be derived from the hospital financial administration. For single-use catheters, this is equal to the purchase price of the catheters. For reusable catheters,

costs of e.g. cleaning also need to be taken into account. This will be based on the time it takes plus possibly material to prepare a reusable catheter to be used again. This information will be estimates based on e.g. observations and/or expert opinion.

The data collected on healthcare utilization will be multiplied by standard unit cost prices, which are described in the Dutch costing manual.

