#### 5.1.2 Urine cultures

Urine samples are obtained and cultured at inclusion (week 0) and final visit (week 52). Significant bacteriuria and thereby a positive urine culture was defined by microbial growth of  $\geq 10^3$  cfu/mL of one or more bacterial species in a single catheter urine specimen or in a mid-stream voided urine specimen, following the European Urology Guidelines on Urological Infections.

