## 5.3.9 Changes in urine cultures over time

Changes in urine cultures over time refers to the evaluation of the bacterial composition of urine samples collected at week 0 (baseline) and week 52 (final visit). This outcome will focus on identifying any changes in bacterial species present in the urine.

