## STATISTICAL ANALYSIS PLAN for COMPaRE-trial

---

|                                     |                                          |                                        |
|-------------------------------------|------------------------------------------|----------------------------------------|
| Episodes of macroscopic hematuria   | During trial                             | Dichotomous                            |
| Hospitalisation, not study linked   | During trial                             | Dichotomous                            |
| Urethral irritation                 | During trial                             | Dichotomous                            |
| Pyelonefritis                       | During trial                             | Dichotomous                            |
| ISCQ-score (patient satisfaction)   | During trial (4 time points)             | Continuous                             |
| InCaSa-score (patient satisfaction) | During trial (4 time points)             | Continuous                             |
| SF-Qualiveen                        | During trial (4 time points)             | Continuous                             |
| Index and EQ VAS-score (QoL)        | During trial (4 time points)             | Continuous                             |
| QALYs and total costs               | During trial                             | Continuous                             |
| Patient opinion (Likert scale)      | Baseline and final visit                 | Categorical                            |
| Changes in urine cultures (S)AE     | Baseline and final visit
During trial | Dichotomous
Categorical/dichotomous |

---

---

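### The SAP's only analysis of urine cultures is a table of common bacteria, which would not answer the protocol's question about reuse, although the paired cultures could

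*Combined protocol and SAP*

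**What the plan says.** Protocol section 2, secondary objective 3: "To determine whether reuse of catheters leads to changes of the urine cultures/urinary microbiome". This point deals with the culture part. Protocol 8.1.2 repeats the question and has catheterised urine samples handed in at the two clinical visits, and protocol 10.2 lists "changes in urinary culture/urinary microbiome" among the secondary outcomes without a method.

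The SAP supplies several of the pieces that a comparison needs:

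- SAP 5.1.2 sets culture at week 0 and week 52 and gives a threshold: "Significant bacteriuria and thereby a positive urine culture was defined by microbial growth of" at least 10^3 cfu/mL of one or more species.
- SAP 5.3.9 defines the outcome as change between the two samples: "This outcome will focus on identifying any changes in bacterial species present in the urine".
- The SAP overview of outcomes places culture change at baseline and final visit and types it as dichotomous (its row runs into the (S)AE row; the types are read in order).

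The whole analysis, in SAP 6.2.3.1, is: "The most common bacteria will be showed in a table for both baseline and end of study". SAP 6.2.3.2 adds that missing data are not imputed.

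The one other relevant line is in protocol 10.1, under primary parameters: "Binomial or categorical outcome measures will be analyzed using Chi-square tests".

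**The concern.** The objective is about the effect of reuse, so it needs a contrast between the randomised arms. The stated analysis is a list of frequent species at two times. If it is carried out as written, the report will hold no estimate of what reuse does to cultures and no interval to show how large an effect remains possible. The dichotomous outcome in the SAP's own overview would not be used.

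Bacterial contamination of the reused catheter is the route by which the protocol's introduction says reuse might raise symptomatic infections and other complications. A reader will look to the culture data for evidence on that route, and a descriptive table could not support a statement of change or of no change.

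**Working it through.** The plan gives no sample size, power or effect size for cultures, so there is no figure of its own to reproduce. The check has two parts.

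**1. What the objective needs against what is specified**

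- Contrast between arms: needed by objective 3. SAP 6.2.3.1 does not mention arm. Elsewhere the SAP names the arm split where it wants one: baseline characteristics (4.2), adherence (4.4.1) and adverse events (6.1.4.1 and 7.1).
- Within-patient link: needed for change as described in SAP 5.3.9. A table of species at each time does not provide it. If *b* patients turn from negative to positive and *c* from positive to negative, the net change in the number positive is *b* − *c*. With *b* = *c* that count does not move, however many patients changed.
- Yes/no variable: typed as dichotomous in the overview. The positivity threshold is defined, but nothing says which pairs of cultures count as a change.
- Estimate and interval: none in SAP 6.2.3. The *Descriptive Statistics* heading does not explain this, because SAP 6.2.1.1 has the same heading and specifies a mixed model with a treatment-by-time interaction.
- Chi-square line in protocol 10.1: it is generic, does not name cultures, and is not carried into SAP 6.2.3. It would give a p-value without an effect size, would not use the baseline culture, and would first need the missing definition of change.

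**2. What the scheduled samples could deliver**

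Inputs:

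- Patients per arm, *n* = 154: the effective cases per group in protocol 4.4. This agrees with the planned enrolment: 386/2 = 193, and 193 × 0.80 = 154.4. It was derived for the sUTI proportion, so its use for week-52 cultures is an assumption.
- Week-52 positivity, *p*: not in the documents. Assumed range 50% to 80%, the same in both arms.

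Half-width of the 95% CI for the difference in positivity, without baseline adjustment: 1.96 × √(2*p*(1 − *p*)/*n*).

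- *p* = 0.5: 1.96 × √(0.50/154) = 0.112
- *p* = 0.6: 1.96 × √(0.48/154) = 0.109
- *p* = 0.7: 1.96 × √(0.42/154) = 0.102
- *p* = 0.8: 1.96 × √(0.32/154) = 0.089

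The formula is symmetric about 50%, so 30% gives the same value as 70%. If all 193 per arm gave a week-52 culture, the half-width would be 10.0 points at 50% and 8.0 at 80%. With fewer than 154 it widens in proportion to 1/√*n*.

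**The case against.** The strongest reply is that the SAP treats cultures as descriptive. They do not appear in its objectives table (2.3.2), SAP 5.3.9 speaks of species present, and a species table fits that wording. The SAP also says in 2.1 that it supplements the protocol, so the chi-square line in protocol 10.1 can be read as covering a dichotomous culture outcome. This stands in part: a reader should not infer that the combined documents rule out any between-arm test. It does not close the gap, because that line cannot be run on an undefined variable and gives no size of effect.

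Three other strong readings are tempting and not supported:

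- *The arms will be pooled.* SAP 6.2.3.1 is silent on arm. A table by arm is a natural reading given the SAP's practice elsewhere. Even so, it would be a descriptive display without pairing or an interval.
- *The objective cannot be answered from the data.* Two cultures per patient in randomised arms, with a stated threshold, are enough for an estimate. The gap is in the analysis plan.
- *Week-52 positivity is the right endpoint by itself.* A patient who is positive at both visits with a new species would count as unchanged, yet that is the kind of change SAP 5.3.9 describes. Positivity needs the paired table beside it.

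It is also fair to say that the clinical consequences of contamination are measured directly: UTI is the primary outcome, and strictures and stones are secondary outcomes. Cultures speak to mechanism.

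**Conclusion.** The point holds for the analysis plan. As specified, SAP 6.2.3.1 would not answer secondary objective 3, because it gives no stated arm split, no link between a patient's two cultures, no definition of the dichotomous variable, and no between-arm estimate or interval.

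The scheduled samples could give an arm difference in positivity to within about 9 to 11 percentage points. That rests on two assumptions: positivity of 50% to 80%, for which the documents give no rate, and 154 week-52 cultures per arm. It is before any gain from baseline adjustment.

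A reader might infer that this weakens the main result. It does not: the decision rule in SAP 3.3.3 rests on UTIs per month alone. The change is worth making for a secondary objective.

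**What to change.** Amend SAP 6.2.3 as follows:

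- (a) State that the species table is presented by arm at both time points.
- (b) Add a by-arm paired-change table with the categories negative to positive, positive to negative, new species, and unchanged. Derive the dichotomous change variable from it, so that it matches SAP 5.3.9. State how a patient who loses one species and keeps another is classed. Keep the full table beside the yes/no variable, because the latter mixes gains and losses.
- (c) Report the between-arm risk difference with 95% CI for week-52 positivity under the 10^3 cfu/mL rule, adjusted for the baseline culture result, for example from a logistic model with standardised risks. Keep other covariates few: the randomisation factors (centre, cause, age bands, gender, menopausal status) could make a binary model unstable. Report a risk difference with 95% CI for the change variable as well. Label both exploratory.
- (d) Report missing week-52 samples by arm, with reasons. Follow-up ends at withdrawal (protocol 8.6), persistent incorrect cleaning leads to exclusion (protocol 8.4.1), which can arise only with reusable catheters, and nothing is imputed. The week-52 cultures may therefore come from differently selected patients in the two arms.

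The cost is a small model, a second simple contrast and one extra table, with no new sampling. The downside is additional exploratory comparisons, which the label makes plain.

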### **6.2.3.2 Missing Data**

Missing data will not be imputed.

## **6.3 Sample size**

The number of studies that have investigated the effects of single use and disposable catheters is limited. Our initial sample size calculation was based on data from a Cochrane review by Prieto et al. (2015), which was later found to contain inaccuracies in data selection and extraction (10).

Specifically, six of the eight trials included in the review did not contain consistent or accurate data compared to their originally published versions. Unfortunately, these erroneous data were used as the basis for our initial sample size calculation (n=456). We were therefore required to perform a new sample size calculation based on the revised 2021 Cochrane review with corrected data (11). The revised Cochrane review included ten studies comparing single-use catheters to reusable catheters. To prevent confounding effects related to insertion techniques (clean vs. sterile), six of these studies employed the same insertions method in both study arms. Among these, three studies provided usable data regarding the number of sUTI events in each group. For single use 18 events out of 68 were observed, for reusable 20 events out of 69. This leads to the proportions of 0.26 and 0.29. Further we applied a power of 0.80 and a one-sided alpha of 0.025 (it is customary to adjust one-sided alphas to the half of 0.05). In our previous calculation, the non-inferiority margin had been determined based on 50% of the mean proportions, following the recommendation of Althunian et al. (12) However, with the corrected data, this would have resulted in an increase in the

# STATISTICAL ANALYSIS PLAN for COMPaRE-trial

---

noninferiority margin to 14%. As this was deemed inappropriate, we opted to maintain the margin at 11%. The sample size is then calculated with:  $n = ((Z(1-\alpha) + Z(1-\beta))^2 [ps(1-ps) + pe(1-pe)]) / ((ps-pe-d)^2)$ , the formula developed by Blackwelder et al in 1982 (13), leading to 154 effective cases in each group. Anticipating a dropout of 20% (14), this must be divided by 80% and rounded upwards. This results in 2 times 193 participants, a total of 386. Because the lack of comparable non-inferiority designed trials with the same primary outcome measurement (sUTI) it is chosen to look at non-inferiority trials with a primary outcome measurement of (treatment of) sUTI. All these trials handled a non-inferiority margin of 10% (15-19), and two trials even 15% (20,21). The head researchers and clinicians of the departments of urology and medical microbiology agreed on the 11% margin to be clinically acceptable. In addition, we encountered the unique challenge of conducting a study with a significantly extended follow-up period of one year, in contrast to the previous studies used in the sample size calculation above, with a shorter follow-up of 2-4 months. Recognizing the impact of time on the occurrence of urinary tract infections (UTIs) and the need to account for this extended observation period, we also performed a sample size calculation that considered the monthly UTI rates observed by Vapnek et al. (22) his calculation factored in not only the proportion of UTIs but also the temporal aspect, recognizing that the incidence of UTIs may vary over time. Vapnek et al. found that single-use catheters had an average of 0.13 UTIs per month (SD 0.18) and multiple-use catheters had an average of 0.14 UTIs per month (SD 0.21) per patient (23). We applied the same power of 0.80 and an one-sided alpha of 0.025. A non-inferiority margin of 7% has been determined based on 50% of the means following the recommendation of Althunian et al. (24) We used the most conservative standard deviation of 0.21 and the sample size calculation was performed using the formula developed by Julious:  $n = f(\alpha, \beta) \times 2 \times \sigma^2 / d^2$  (245). This calculation led to a requirement of 152 effective cases in each group. Anticipating a dropout rate of 20%, this figure was divided by 0.80, resulting in a total sample size of 382 participants (191 in each group). Since the sample size of 382 is almost equal to our sample size that does not correct for time ( $n=386$ ), we will include 386 participants to account for both methods.

Sample size: 386 patients.

## 7 Safety Analyses

General safety evaluations will be based on the incidence and type of AEs. Safety variables will be tabulated and presented for all patients in the safety set. Safety analysis will be presented in the primary outcomes manuscript.

### 7.1 Adverse Events

Adverse events are defined as any undesirable experience occurring to a subject during the study, whether or not considered related to the investigational product. All adverse events reported spontaneously by the subject or observed by the investigator or his staff will be recorded.

The number (%) of subjects with any AEs will be summarised by treatment group. SAEs will be detailed and presented in a separate table. Adverse events will be presented in the primary outcomes manuscript.

### 7.2 Clinical Laboratory Parameters

Not applicable

## 7.3 Vital Signs

Not applicable

## 8 Statistical Software

All statistical analyses will be performed using R (R Core Team, 2023. R: A language and environment for statistical computing, version 4.4.1. R Foundation for Statistical Computing, Vienna, Austria. URL: <https://www.R-project.org>).

